### 15.2.1 Immediate Reporting of Serious Adverse Events

In order to adhere to all applicable laws and regulations for reporting an SAE, the study site must formally notify [REDACTED] within 24 hours of the study site staff becoming aware of the SAE. It is the Investigator's responsibility to ensure that the SAE reporting information and procedures described in Figure 15-1 are used and followed appropriately.

#### 15.2.1.1 Death

The death must be recorded on the appropriate CRF. All causes of death must be reported as SAEs. The Investigator should make every effort to obtain and send death certificates and autopsy reports to [REDACTED]

If a subject's treatment assignment is unblinded for a medical emergency that ultimately leads to death, the Investigator must also document the reasons for the unblinding in the subject's CRF. *The Investigator is strongly advised not to divulge the subject's treatment*

*assignment to any individual not directly involved in managing the medical emergency nor to personnel involved with the analysis and conduct of the study.*

### Figure 15-1. Reporting Information for SAEs

Any SAE that occurs after the subject signs the ICF until Visit 12/Week 26 must be reported to [REDACTED] within 24 hours of the study site staff becoming aware of the event. This report must be submitted regardless of whether or not the subject has undergone any study-related procedures or received study treatment and *regardless of severity or relationship to study treatment.*

To report initial or follow-up SAE information, fax a completed SAE form to the following:

[REDACTED]

## 15.3 Safety Classifications

### 15.3.1 Relationship of Events to Study Treatment

The following definitions should be considered when evaluating the relationship of AEs and SAEs to the study treatment:

#### ***Relationship of Event to Study Treatment***

|           |                                                                                                                                                                                                                                                                                                                                             |
|-----------|---------------------------------------------------------------------------------------------------------------------------------------------------------------------------------------------------------------------------------------------------------------------------------------------------------------------------------------------|
| Unrelated | Any event that does not follow a reasonable temporal sequence from administration of study treatment AND that is likely to have been produced by the subject's clinical state or other modes of therapy administered to the subject.                                                                                                 |
| Unlikely  | Any event that does not follow a reasonable temporal sequence from administration of study treatment OR that is likely to have been produced by the subject's clinical state or other modes of therapy administered to the subject.                                                                                                  |
| Possibly  | Any reaction that follows a reasonable temporal sequence from administration of study treatment OR that follows a known response pattern to the suspected drug AND that could not be reasonably explained by the known characteristics of the subject's clinical state or other modes of therapy administered to the subject. |
| Related   | Any reaction that follows a reasonable temporal sequence from administration of study treatment AND that follows a known response pattern to the suspected drug AND that recurs with re-challenge, AND/OR is improved by stopping the drug or reducing the dose.                                                       |

CONFIDENTIAL

The information contained herein may not be used, disclosed, or published without the written consent of  
Biogen Idec Inc.

### 15.3.2 Severity of Events

The following definitions should be considered when evaluating the severity of AEs and SAEs:

#### **Severity of Event**

|          |                                                                                                                                                                                                                                                     |
|----------|-----------------------------------------------------------------------------------------------------------------------------------------------------------------------------------------------------------------------------------------------------|
| Mild     | Symptom(s) barely noticeable to subject or does not make subject uncomfortable; does not influence performance or functioning; prescription drug not ordinarily needed for relief of symptom(s) but may be given because of personality of subject. |
| Moderate | Symptom(s) of a sufficient severity to make subject uncomfortable; performance of daily activity is influenced; subject is able to continue in study; treatment for symptom(s) may be needed.                                                       |
| Severe   | Symptom(s) cause severe discomfort; symptoms cause incapacitation or significant impact on subject's daily life; severity may cause cessation of treatment with study treatment; treatment for symptom(s) may be given and/or subject hospitalized. |

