### **15.1 Definitions**

#### **15.1.1 Adverse Event**

An AE is any untoward medical occurrence in a patient or clinical investigation subject administered a pharmaceutical product and that does not necessarily have a causal relationship with this treatment. An AE can therefore be any unfavorable and unintended sign (including an abnormal laboratory finding), symptom, or disease temporally associated with the use of a medicinal (investigational) product, whether or not related to the medicinal (investigational) product.

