## 15.2 Monitoring and Recording Events

Any SAE experienced by the subject from the time the subject signs the ICF until the End of Study Visit, and any non-serious AE experienced by the subject after time of first dose until the End of Study Visit (see Section 7.2), is to be recorded on the CRF, regardless of the severity of the event or its relationship to study treatment. Instructions will be provided separately in the CRF Completion Guidelines.

Any AE or SAE ongoing when the subject completes the study or discontinues from the study will be followed by the Investigator until the event has resolved, stabilized, or returned to baseline status.

All events must be assessed to determine the following:

- If the event meets the criteria for an SAE as defined in Section 15.1.2.
- The relationship of the event to study treatment as defined in Section 15.3.1.
- The severity of the event as defined in Section 15.3.2.

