#### *Clinical Adverse Events*

Only treatment-emergent AEs will be presented in the summary tables. Treatment-emergent is defined as having onset date that is on or after start of study treatment, or that is worsened after the start of study treatment.

Incidence of treatment-emergent AEs will be summarized by treatment groups, overall, by severity, and by relationship to study treatment. The summary tables will include incidence estimates for overall system organ class as well as for preferred terms within each system organ class.

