## **19.2 Study Committees**

### **19.2.1 Data Monitoring Committee**

An independent Data Monitoring Committee (DMC) will be formed to review interim safety data. Members of the DMC will not be allowed to participate as Investigators in this study and will not be affiliated in any way with Biogen Idec.

The DMC will review unblinded ongoing safety data on a quarterly basis to ensure the safe and proper treatment of a subject, or if the severity of an AE(s), if study treatment related, would lead to early termination of the study. The DMC will advise on the continuing safety of the study, along with the continuing validity and scientific merit. A DMC Charter will provide full guidance on the function and practices to be followed by the Committee. Investigational sites will be notified of any relevant safety findings that may jeopardize subject safety.

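### The protocol's only severity scale (15.3.2) has no criterion for laboratory adverse events, so the by-severity summary may understate marked but symptom-free abnormalities

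*Protocol*

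**What the plan says.** Protocol 15.1.1 defines an adverse event to include any "unfavorable and unintended sign (including an abnormal laboratory finding), symptom, or disease". Protocol 15.2 states that "All events must be assessed to determine the following", and one item on its list is "The severity of the event as defined in Section 15.3.2". No other severity scale appears in the protocol.

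The text introducing that scale says "The following definitions should be considered when evaluating the severity of AEs and SAEs". The lowest grade is "Symptom(s) barely noticeable to subject or does not make subject uncomfortable; does not influence performance or functioning", with the further remark that prescription medicine is not usually needed to relieve the symptoms. Moderate and Severe also begin with symptoms and their effect on comfort and daily life. Moderate adds that the subject can stay in the study. Severe adds possible cessation of study treatment and possible hospitalization.

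The grade feeds a planned table, in 16.2.5.2 (Clinical Adverse Events): "Incidence of treatment-emergent AEs will be summarized by treatment groups, overall, by severity, and by relationship to study treatment". Laboratory results are handled separately in the same section by shift tables. In 19.2.1 the Data Monitoring Committee (DMC) is asked to consider "if the severity of an AE(s), if study treatment related, would lead to early termination of the study".

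**The concern.** A scale built on how the subject feels cannot rank an event that the subject does not feel. Liver enzyme rises and falls in neutrophils can be silent, and the study drug is an immune-modulating agent given on top of methotrexate. If a small and a large silent abnormality both attract the lowest grade, the by-severity summary loses the information it exists to show. The loss would be greatest in whichever regimen causes most laboratory toxicity. Safety and tolerability of the five regimens is a secondary objective (6.2), and the study is meant to support dose selection (5.3), so a safety table that blurs differences between arms matters.

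**Working it through.** The point is one of definition. The protocol gives no figure to reproduce, so the sections are set side by side.

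**Step 1: is a silent laboratory abnormality an adverse event?** It can be. Protocol 15.1.1 says "An AE can therefore be any unfavorable and unintended sign (including an abnormal laboratory finding), symptom, or disease". No symptom is required.

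**Step 2: must it be graded, and on what?** Yes. Protocol 15.2 applies to all events and points to 15.3.2.

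**Step 3: apply the scale.** Take two hypothetical subjects without symptoms, one with ALT at 2 times and one at 12 times the upper limit of normal (ULN). These values are assumed for illustration.

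| Grade | What the wording turns on | ALT 2 x ULN | ALT 12 x ULN |
|---|---|---|---|
| Mild | no discomfort, no effect on functioning | fits | fits |
| Moderate | uncomfortable symptoms, daily activity affected | opening criterion not met | opening criterion not met |
| Severe | severe discomfort or incapacity; treatment cessation and hospitalization also named | opening criterion not met | opening criterion not met; arguable only if treatment is stopped or the subject is hospitalized |

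No grade refers to a laboratory value, a multiple of ULN or medical significance. The route through cessation or hospitalization grades the action taken and not the value. The text also leaves open whether those items are alternatives to the symptom wording or additions to it.

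**Step 4: where does the grade go?** Into the by-severity summary of treatment-emergent events in 16.2.5.2, for each of the six arms.

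**Step 5: do the laboratory tables make up for it?** In part. The Laboratory Data part of 16.2.5.2 specifies shifts to high or low status, and shifts to the maximum and minimum post-baseline result for each test by arm. Summary statistics are optional, and the Synopsis adds the proportion of subjects outside the normal range. None of these sets magnitude bands. The protocol does use numeric limits elsewhere: for vital signs in Table 16-2, and at entry for AST/ALT, platelets, hemoglobin and neutrophils in 8.2.

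**Step 6: what would one under-graded subject do to the table?** From 16.4, 380 subjects are randomized 2:2:2:2:1:1, which is 10 parts.

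- Placebo and every-other-week arms: 380 x 2/10 = 76 subjects. One subject is 1/76 = 1.3%.
- Monthly arms: 380 x 1/10 = 38 subjects. One subject is 1/38 = 2.6%.
- If 1 to 3 subjects in an arm had a marked silent abnormality graded Mild (an assumption; the protocol gives no rate), the shortfall in the higher grades would be 1.3 to 3.9 percentage points in a 76-subject arm (3/76 = 3.9%) and 2.6 to 7.9 points in a monthly arm (3/38 = 7.9%).

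**The case against.** The strongest reply is that the scale guides and does not bind. The definitions are only to be considered, and 15.6 makes the investigator responsible for determining severity. A sensible investigator may grade a large silent ALT rise above Mild. Mild itself begins with barely noticeable symptoms, so a finding with no symptoms is not squarely covered. Severe mentions stopping study treatment and hospitalization, which gives some laboratory events a route upward. All of this stands. It turns a fixed wrong grade into grading that leans toward Mild and varies across about 60 sites (7.1).

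A reader might infer more: that every silent laboratory event is Mild by definition, that it vanishes from a severe-event table, and that the DMC would be misled. The protocol does not support these readings.

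- The wording leaves judgement, as above.
- No separate severe-event table is named. The event stays in overall incidence under a lower grade, remains visible in the laboratory shifts, and can be a serious event as medically important (15.1.2).
- The DMC reviews unblinded safety data quarterly under its own charter, and its use of the word severity in 19.2.1 is not tied to the 15.3.2 grade.

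A further reply is that graded laboratory tables can be left to the statistical analysis plan. That holds for the tables. It does not hold for the rule under which sites assign the grade, because that rule is fixed in the protocol. Finally, the account of earlier studies in 5.2 reports no hepatic or neutropenic signal. This bears on how often the problem would arise, not on whether the scale can grade it.

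**Conclusion.** The concern holds in this form: abnormal laboratory findings must be graded on a scale that contains no laboratory criterion. Read as written, a marked but symptom-free abnormality fits Mild and has no clear route higher unless treatment is stopped or the subject is hospitalized. The by-severity summary may therefore understate silent hepatic or hematologic toxicity, and the shift tables compensate only in part.

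The size is unknown. It depends on how often such abnormalities occur and how investigators use their discretion, and the protocol informs neither. The per-subject effect in Step 6 is simple arithmetic on the planned arm sizes; the range of 1 to 3 subjects is an assumption and not a forecast. The primary efficacy analysis is not affected. The point is worth correcting before sites begin grading, because the wording governs the data at source.

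**What to change.** In 15.3.2, add that the severity of an adverse event that is a laboratory finding is judged by the laboratory value against pre-specified numeric bands and not by symptoms. List the bands in a short table: multiples of ULN for AST, ALT, bilirubin and creatinine, and absolute bands for hemoglobin, neutrophils, white cells and platelets. Keep the present scale for clinical events.

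Keep the investigator's grade as the recorded severity. Replacing it by program would conflict with 15.6. Beside it, add a program-derived laboratory severity summary by treatment group, computed from the central-laboratory data, to the safety tables in 16.2.5.2 and to the DMC outputs. If lymphocytes are included, that summary must not reach the sites, because 9.3 and 13.2 withhold lymphocyte counts to protect the blind.

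The cost is modest. No extra tests or visits are needed. The sponsor must choose the band limits, reported laboratory events must be matched to a test result and visit, and some laboratory events will move to a higher grade.

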### 15.4 Prescheduled or Elective Procedures or Routinely Scheduled Treatments

A prescheduled or elective procedure or a routinely scheduled treatment shall not be considered an SAE, even if the subject is hospitalized, provided the site stipulates the following:

- The prescheduled or elective procedure or routinely scheduled treatment was scheduled (or was on a waiting list to be scheduled) prior to obtaining the subject's consent to participate in the study.
- The condition requiring the prescheduled or elective procedure or routinely scheduled treatment was present before and did not worsen or progress between the subject's consent to participate in the study and the time of the procedure or treatment.
- The prescheduled or elective procedure or routinely scheduled treatment is the sole reason for the intervention or hospital admission.

### 15.5 Procedures for Handling Special Situations

#### 15.5.1 Medical Emergency

In a medical emergency requiring immediate attention, study site staff will apply appropriate medical intervention, according to current standards of care, and contact the [REDACTED]. In all cases, the [REDACTED] must be informed when a subject's treatment code has been unblinded.

#### 15.5.2 Pregnancy

If a female subject becomes pregnant, study treatment must be discontinued *immediately*.

The Investigator must report the pregnancy by faxing the appropriate form to [REDACTED] within 24 hours of the study site staff becoming aware of the [REDACTED]

CONFIDENTIAL

The information contained herein may not be used, disclosed, or published without the written consent of  
Biogen Idec Inc.

pregnancy, [REDACTED]  
[REDACTED] The Investigator or study site staff must report the outcome of the pregnancy to [REDACTED]

### 15.5.3 Unblinding

In this study, emergency decoding will be made available to the Investigator and designated personnel at Biogen Idec [REDACTED] through IVRS.

In a medical emergency when knowledge of the subject's treatment assignment may possibly influence the subject's clinical care, the Investigator may access the subject's treatment assignment via IVRS. However, prior to unblinding, the Investigator should attempt to contact the [REDACTED] to discuss the emergency whenever possible.

The Investigator must document the reasons for unblinding in the subject's source documents. *The Investigator is strongly advised not to divulge the subject's treatment assignment to any individual not directly involved in managing the medical emergency nor to personnel involved with the analysis and conduct of the study.*

#### 15.5.3.1 Accidental Unblinding

If a subject's treatment assignment is unblinded, the subject must immediately discontinue study treatment. The subject should remain in the study and complete the study-specific follow-up tests and assessments (Week 14 to Week 26).

#### 15.5.3.2 Unblinding for Reporting Purposes

Upon receipt of an unexpected SAE considered to be related or possibly related to the study treatment by the Investigator or the Sponsor (see Section 15.1.3), Biogen Idec DSRM or its designee will unblind the subject's treatment assignment. Regulatory authorities and central ethics committees will be notified of the event(s) when applicable, in accordance with local laws and regulations.

### 15.6 Investigator Responsibilities

The Investigator's responsibilities include the following:

- Monitor and record all AEs, which includes SAEs, regardless of the severity or relationship to study treatment.
- Determine the seriousness, relationship, and severity of each event.
- Determine the onset and resolution dates of each event.
- Monitor and record all pregnancies and follow-up on the outcome of the pregnancy and status of the infant.

- Complete an SAE form for each SAE and fax it to [REDACTED] within 24 hours of the study site staff becoming aware of the event.
- Pursue SAE follow-up information actively and persistently. Follow-up information must be reported to [REDACTED] within 24 hours of the study site staff becoming aware of new information.
- Ensure all AE and SAE reports are supported by documentation in the subjects' medical records.
- For sites using a local ethics committee, notify the ethics committee as per ethics committee requirements, of any SAEs. A copy of ethics committee notification must also be sent to your Clinical Monitor in a timely manner.

### **15.7 Biogen Idec Responsibilities**

Biogen Idec's responsibilities include the following:

- Before study site activation and subject enrollment, the Biogen Idec or designee is responsible for reviewing with study site staff the definitions of AE and SAE, as well as the instructions for monitoring, recording, and reporting AEs and SAEs.
- Biogen Idec or designee is to notify all appropriate regulatory authorities, central ECs, and Investigators, of SAEs as necessary, within the required time frames and in accordance with local regulations. Biogen Idec is to complete written safety reports, with the information provided by the Investigator and study site staff, as needed, for submission to regulatory authorities and central ECs.

## **16 STATISTICAL STATEMENT AND ANALYTICAL PLAN**

### **16.1 Description of Objectives and Endpoints**

#### **16.1.1 Primary Objective and Endpoints**

The primary objective of the study is to evaluate the efficacy of 4 dose regimens of BG9924 when administered in combination with MTX to subjects with active RA who have had an inadequate response to conventional DMARD therapy.

The primary efficacy endpoint is the proportion of subjects with ACR50 at Week 14.

The secondary efficacy endpoints will be:

- the proportion of subjects with an ACR20 and ACR70 at Week 14,
- the change from baseline in Quality of Life (HAQ-DI, SF-36, FACIT-F) at Week 14,
- the change from baseline DAS28 at Week 14,
- the proportion of subjects with a categorical DAS28 response (EULAR response) at Week 14, and

---

CONFIDENTIAL

The information contained herein may not be used, disclosed, or published without the written consent of Biogen Idec Inc.

- changes from baseline in the individual ACR core set parameters at Week 14.

### **16.1.2 Secondary Objectives**

Secondary objectives of this study are as follows:

- To assess the safety and tolerability of these 4 dose regimens of BG9924 in this patient population.
- To assess the PK and PD profile of these 4 dose regimens of BG9924 in this patient population.

### **16.1.3 Exploratory Endpoints**

The exploratory endpoints are:

- ACR responses over time (including ACRn)
- Change in Sjogrens assessments in subjects with Sjogrens syndrome: subject-reported dryness including VAS (ocular, vaginal, skin, and oral) and OSDI.

## **16.2 Criteria for the Endpoints**

All statistical tests will be 2-sided with a type I error rate of 5%. Formal statistical comparisons for efficacy endpoints will be made between each BG9924 dose group versus placebo. No adjustments will be made for multiple comparisons.

Subjects with missing efficacy measurements at the visit being analyzed will be considered treatment failures for that visit. Subjects who require rescue interventions (Section 11.4) will be considered a non-responder for all analysis time points subsequent to usage of the rescue medication. Missing values for continuous endpoint values will be replaced using last observation carried forward (LOCF).

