## **7 STUDY DESIGN**

### **7.1 Study Overview**

This is a randomized, double-blind, placebo-controlled, multicenter, dose-finding study of BG9924 in subjects with active RA who have had an inadequate response to conventional DMARD therapy. Approximately 380 subjects will be enrolled at approximately 60 sites. Subjects may participate in this study for up to 26 weeks. Over the treatment period, subjects will receive BG9924 (1 of 5 dosing regimens) or placebo by SC injection, every other week for 12 weeks (including a loading dose, with the first half given at Week 0 and second half at Weeks 1 or 2), with a follow-up visit 2 weeks after the last dose (Visit 9/Week 14). Subjects who continue in the study until Week 14 will be offered the option to enter a safety extension study (under a separate protocol). Subjects who do not enroll in the extension study will be followed for safety assessments for an additional 12 weeks (until Visit 12/ Week 26) under this protocol.

Study sites may choose to participate in an optional PK sub-study. Approximately 50 consenting subjects will have 6 additional visits for blood draws following Visits 1 (Visits 1a and 1b), 3 (Visit 3a), and 8 (Visits 8a, 8b, and 8c). Blood samples for FACS analysis will also be taken from subjects participating in this sub-study.

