### ***Post-Treatment Period***

Subjects are to return to the study site for a follow-up visit at Week 14 (Visit 9, 2 weeks after the last dose) for primary endpoint evaluations. At this visit, subjects will be offered the option to enter a safety extension study, under a separate protocol. Subjects who do not enroll into the safety extension study will be followed for an additional 12 weeks (until Visit 12/Week 26) under this protocol. Therefore, the final visit will be either Visit 9/Week 14 or Visit 12/Week 26, depending on whether subjects choose to enroll in the safety extension study.

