#### **14.2.13 Visit 9 (Week 14, Day 98 $\pm$ 3; primary endpoint evaluation, option to enter extension study, and early withdrawal visit [withdrawal prior to Week 14])**

- Physical examination
- Vital signs: temperature, heart rate, respiratory rate, and supine blood pressure (after 5 minutes' rest)
- ACR core set measurements (see Section 12.1 for list of measurements)

- QoL (SF-36, FACIT-F)
- Sjogrens assessments (see Section 12.1 for assessments), if applicable
- Blood samples collected for:
  - hsCRP and ESR (ESR to be performed at local laboratory)
  - RF and anti-CCP-2 antibody
  - RA Disease Markers (serum BAFF, COMP, calgranulin, and MMP3)
  - Quantitative FACS analysis, only in subjects participating in the optional PK sub-study (see Section 12.4 for list of variables)
  - Cytokine panel (see Section 12.4 for list of variables)
  - Serum BG9924 PK assay
  - Hematology (see Section 13.2 for list of variables)
  - Quantitative Ig (IgA, IgG, and IgM)
  - Blood chemistry (see Section 13.2 for list of variables)
  - INR, PT, and aPTT
  - ANA and anti-dsDNA antibody assays
  - Serum anti-BG9924 antibody assay
  - Tetanus antibody titers
  - RNA Analysis
- Urinalysis (see Section 13.2 for list of variables)
- Urine pregnancy test
- ECG
- Monitoring of AEs/SAEs (see Section 15.2)
- Monitoring of concomitant therapy

Visit 9 (Week 14) evaluations will be completed for all subjects who complete the treatment period or who withdraw from the study prior to Visit 9/Week 14; this will be the last visit for subjects who choose to enter the safety extension study.

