#### **14.2.16 Visit 12 (Week 26, Day 182 ±3; late withdrawal visit [withdrawal after Week 14])**

- Physical examination
- Vital signs: temperature, heart rate, respiratory rate, and supine blood pressure (after 5 minutes' rest)
- ACR core set measurements (see Section 12.1 for list of measurements)
- QoL (SF-36, FACIT-F)
- Sjogrens assessments (see Section 12.1 for assessments), if applicable
- Blood samples collected for:
  - hsCRP and ESR (ESR to be performed at local laboratory)
  - Serum BG9924 PK concentration
  - Hematology (see Section 13.2 for list of variables)
  - Quantitative Ig (IgA, IgG, and IgM)
  - Blood chemistry (see Section 13.2 for list of variables)
  - INR, PT, and aPTT
  - ANA and anti-dsDNA antibody assays (only from subjects with positive ANA/anti-dsDNA at Week 14)
  - Serum anti-BG9924 antibody assay
  - Tetanus antibody titers
- Urinalysis (see Section 13.2 for list of variables)
- Monitoring of AEs/SAEs (see Section 15.2)

- Monitoring of concomitant therapy

Visit 12 (Week 26) evaluations will be completed for all subjects who complete the treatment and post-treatment period, or who withdraw during the post-treatment period.

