#### Exploratory endpoints:

##### ACR responses over time (including ACRn)

To achieve an ACRn response, a n% improvement compared to baseline is required for both swollen and tender joint counts, as well as 3 out of 5 additional parameters: subject's global assessment of disease activity, Investigator's global assessment of disease activity, subject's assessment of pain, HAQ-DI, and hsCRP or ESR.

Summary statistics of ACR responses over time (including ACRn) will be presented.

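### The missing-means-failure rule in 16.2 has no visit limit, so ACR summaries after Week 14 would count extension entrants as failures; crude AE incidence likewise mixes 14-week and 26-week follow-up

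*Protocol*

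**What the plan says.** **Missing data.** Protocol 16.2 gives two rules. For responder endpoints: "Subjects with missing efficacy measurements at the visit being analyzed will be considered treatment failures for that visit". For continuous endpoints, missing values are filled by LOCF. Neither rule names a last visit or makes an exception for subjects who move to the extension.

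**Who has data after Week 14.** Section 14.2.13 says of Visit 9 that "this will be the last visit for subjects who choose to enter the safety extension study". For the rest, section 7.2 says "Subjects who do not enroll into the safety extension study will be followed for an additional 12 weeks". Sections 14.2.14 to 14.2.16 schedule the ACR core set at Weeks 18, 22 and 26. Sections 11.2.1 and 15.5.3.1 also direct subjects who stopped treatment early, or were accidentally unblinded, to follow-up through Week 26.

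**Denominator and endpoint.** The efficacy population in 16.2.4.1 is everyone dosed. ACR response over time is an exploratory endpoint with no end week: "Summary statistics of ACR responses over time (including ACRn) will be presented".

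**Adverse events.** Under 15.2, non-serious AEs are recorded from first dose to the End of Study Visit, which 7.2 places at either Week 14 or Week 26. Section 16.2.5.2 sets a start for the counting window: "Treatment-emergent is defined as having onset date that is on or after start of study treatment" (or worsening after that start). It sets no common end, and summarizes incidence by treatment group without adjusting for length of follow-up.

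**The concern.** Entering the extension is planned continuation, not treatment failure. Applied literally at Weeks 18 to 26, the rule turns a Week 14 responder who continues into a non-responder, while an early discontinuer who attends those visits keeps the observed result. The ACR-over-time display would then fall sharply after Week 14 in every arm, most where most subjects continue, and could be read as loss of response off drug. In a study meant to support dose selection, that is a misleading display of durability.

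The AE issue has the same origin, the split at Week 14, but does not come from the quoted rule. Length of AE follow-up depends on a choice made after randomization. If that choice differs by arm, crude incidence compares unequal observation time, and the arm that continues more shows fewer events for that reason alone. Safety and tolerability of the regimens is a secondary objective.

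**Working it through.** **1. The plan's own figure.** Section 16.4 gives 380 subjects at 2:2:2:2:1:1, 15% dropout, Week 14 ACR50 of 42% v 15%, and power of 90% (every other week) and 74% (monthly) by Fisher's exact test.

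- Group sizes: 380 × 2/10 = 76 and 380 × 1/10 = 38. After dropout: 76 × 0.85 = 64.6 and 38 × 0.85 = 32.3.
- Exact enumeration, Fisher's test with 2.5% in the favourable tail: 90.6% (64 v 64) and 91.1% (65 v 65); 74.9% (64 v 32) and 74.3% (65 v 32).
- Dropouts counted as failures with the full 76 and 38: 89.4% and 73.9%.
- A minimum-likelihood two-sided Fisher test gives a higher monthly figure, 78.0% to 80.6%.

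The stated power reproduces. It is a Week 14 figure, and roll-over happens at that visit after the endpoint is assessed, so it does not enter.

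**2. ACR50 at Weeks 18 to 26 under the failure rule.** Assumptions: 42% and 15% apply to subjects observed at Week 14; 15% dropout counts as failure; true response does not change after Week 14; roll-over r is unrelated to response.

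Reported response = p × 0.85 × (1 − r). At r = 0: 0.42 × 0.85 = 35.7% and 0.15 × 0.85 = 12.75%.

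| Roll-over r (assumed) | BG9924 | Placebo | Difference (points) |
|---|---|---|---|
| 0% | 35.7% | 12.8% | 23.0 |
| 25% | 26.8% | 9.6% | 17.2 |
| 50% | 17.9% | 6.4% | 11.5 |
| 75% | 8.9% | 3.2% | 5.7 |
| 90% | 3.6% | 1.3% | 2.3 |

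If 42% and 15% are taken without the dropout factor, 50% roll-over gives 21.0% v 7.5% and 90% gives 4.2% v 1.5%. The proportional loss is the same.

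**3. AE incidence.** Assumptions: the same constant hazard h in both arms through Week 26, no dropout, extension entrants observed for 14 weeks and the others for 26.

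Incidence = r(1 − e^(−14h)) + (1 − r)(1 − e^(−26h)). With h = 0.03 per week, 1 − e^(−0.42) = 34.3% and 1 − e^(−0.78) = 54.2%.

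- r = 90%: 0.9 × 34.3 + 0.1 × 54.2 = 36.3%.
- r = 70%: 0.7 × 34.3 + 0.3 × 54.2 = 40.3%.
- Equal r in both arms: equal incidence, no distortion.

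A wider gap does more. If 30% have an event by Week 14 (hence 48.4% by Week 26 at constant hazard), 90% v 50% roll-over gives 31.8% v 39.2%, a ratio of 1.23 with identical hazards. If the hazard fell to zero after Week 14, both arms would stay at their Week 14 incidence whatever the roll-over.

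**The case against.** The best reply is that the plan never says ACR over time runs past Week 14. Section 7.1 describes the later follow-up in these terms: "Subjects who do not enroll in the extension study will be followed for safety assessments for an additional 12 weeks". Section 16.3 runs the analyses when all subjects reach Week 14. For an extension entrant, a Week 18 value was never scheduled, so it need not be called missing, and the visits a descriptive table covers are often fixed in the SAP. This makes the efficacy harm conditional. It does not remove it: the protocol collects the ACR core set at those visits, gives the endpoint no end week, and states a rule that gives a wrong result there. Nor does 16.3 set a per-subject data cut-off. With staggered enrolment, early non-entrants can already have data beyond Week 14 when the last subject reaches it.

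On AEs, it is fair to say that common cut-offs and person-time are ordinary SAP content, that recording does stop at the End of Study Visit, and that nothing in the protocol shows roll-over will differ by arm.

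Three stronger readings are tempting and not supported:

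- *That the main efficacy results are biased.* The primary and all secondary efficacy endpoints in 16.1.1 are at Week 14.
- *That roll-over distorts LOCF for DAS28 and HAQ-DI.* Their stated analyses are at Week 14, which roll-over cannot affect. LOCF past Week 14 could matter only in untimed descriptive summaries, such as the Sjögren's change that is measured again at Week 26. Whether LOCF suits dropout before Week 14 is a separate question.
- *That the AE tables will hide drug-related events.* That needs unequal roll-over and events after Week 14, and the documents give figures for neither.

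**Conclusion.** The point holds in limited form. As written, the failure rule scores extension entrants as non-responders in any all-dosed ACR summary at Weeks 18, 22 or 26, shrinking each reported rate by the factor (1 − roll-over). With no true loss of response, a 23.0-point difference would appear as 11.5 points at 50% roll-over and 2.3 at 90%. These sizes rest on an assumed roll-over rate, unrelated to response, and on unchanged response after Week 14. Only exploratory descriptive summaries are exposed.

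Crude AE incidence over mixed 14-week and 26-week follow-up is a second, separate weakness. It distorts arm comparisons only if roll-over differs by arm: 4.0 points (36.3% v 40.3%) in the 90% v 70% illustration, and none when roll-over is equal.

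The change is worth making because it is cheap and corrects a rule the protocol states outright. It does not call the Week 14 conclusions into question.

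**What to change.** - **In 16.2:** limit the failure rule and LOCF to visits through Week 14. Present Weeks 18, 22 and 26 as observed data, with n at each visit, in subjects who stayed in follow-up under this protocol. Describe that group as those who did not enter the extension, including early treatment discontinuers, and not simply as subjects who declined it.
- **In 16.2.5.2:** have the comparative AE, SAE and infection tables cover first dose to the Week 14 visit in every arm. Tabulate later events separately, with person-time.

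The cost is a few sentences and a little programming, with no new data. Late events move to a second table, so both tables must be read for the full safety picture. The observed Week 18-26 group is also self-selected and should not be compared directly with Week 14. For example, with true rates of 42% v 15%, if responders rolled over at 90% and non-responders at 50%, the observed rates would be 0.042/(0.042 + 0.290) = 12.7% v 0.015/(0.015 + 0.425) = 3.4%. The label and the n are there to keep that visible.
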